## Abstract

**Background/Objectives**: Chronic obstructive pulmonary disease (COPD) remains a major global health problem, affecting over 300 million people worldwide. Its high morbidity and mortality rates impose substantial psychosocial and financial burdens on patients and healthcare systems. In the emergency setting, managing acute exacerbations of COPD (AECOPD) poses a major clinical challenge, as these patients often present with multi-organ dysfunction secondary to hypoxia and hypercapnia. Identifying reliable prognostic biomarkers could improve early risk stratification, guide therapeutic decisions, and enhance patient outcomes. **Methods**: This multicenter, prospective, observational study aims to evaluate the prognostic significance of several novel biomarkers—resistin, club cell secretory protein 16 (CC16), interleukin-6 (IL-6), tumor necrosis factor-alpha (TNF-α), S100β protein—alongside conventional markers such as N-terminal-pro–B-type-Natriuretic-Peptide (NT-proBNP), D-dimer, high-sensitivity troponin I (hs-cTnI), C-reactive protein (CRP), and procalcitonin in patients with AECOPD admitted to the Emergency Department (ED). Blood samples will be collected at admission. The novel biomarkers (resistin, CC16, IL-6, TNF-α, S100β) will be measured using standardized ELISA kits, while conventional biomarkers (NT-proBNP, troponin I, CRP, procalcitonin) will be analyzed using routine automated clinical laboratory methods. Correlations between biomarker levels, clinical and imaging data, severity scores (GCS, SOFA, CFS, Ottawa COPD Risk Scale, DECAF, BAP-65), and short-term outcomes (hospital discharge status and 28-day survival) will be assessed. The study has received approval from the Ethics Committee of the “Iuliu-Hatieganu” University of Medicine and Pharmacy, Cluj-Napoca, and all participating hospitals. Written informed consent will be obtained from all participants or their legal representatives. **Results:** This study protocol does not report results, as data collection and analysis are ongoing. **Conclusions /Expected Impact:** By identifying novel biomarkers with prognostic and pathophysiological relevance, this research aims to inform the development of early risk stratification tools and support future evidence-based approaches to the management of critically ill COPD patients in the ED.

## 1. Introduction

Chronic obstructive pulmonary disease (COPD) represents one of the leading causes of morbidity and mortality worldwide, accounting for substantial healthcare expenditures and social burden. Despite advances in preventive and therapeutic strategies, COPD exacerbations remain a major cause of emergency department (ED) admissions and hospitalizations [1,2]. According to the 2023 Global Initiative for Chronic Obstructive Lung Disease (GOLD) report, COPD is now recognized as a complex, systemic condition extending beyond the respiratory tract, involving inflammatory and metabolic alterations that contribute to multi-organ dysfunction [3].

Acute exacerbations of COPD (AECOPD) are pivotal events in disease progression, often precipitating irreversible declines in pulmonary function, worsening quality of life, and escalating mortality risk. During exacerbations, the systemic inflammatory response becomes amplified, leading to acute respiratory failure and subsequent cardiovascular or neurological complications. Patients admitted to the ED frequently present with hypoxia, hypercapnia, and hemodynamic instability, which may evolve into multi-organ dysfunction. The accurate early assessment of prognosis in this setting remains challenging, as current risk stratification tools, although widely used, including the Modified Medical Research Council (mMRC) scale, the Sequential Organ Failure Assessment (SOFA) score, the Glasgow Coma Scale (GCS), the DECAF score for in-hospital mortality, the BAP-65 score, the Ottawa COPD Risk Scale, and the Clinical Frailty Scale (CFS), do not incorporate objective biological markers of systemic injury or repair [4,5,6,7,8,9].

Recent advances in molecular diagnostics have underscored the potential of circulating biomarkers to reflect the underlying pathophysiological processes of COPD. Several molecules involved in systemic inflammation, oxidative stress, and epithelial injury have emerged as candidates for prognosis and therapeutic guidance. Among these, resistin, club cell secretory protein (CC16), interleukin-6 (IL-6), tumor necrosis factor-alpha (TNF-α), and S100β protein stand out for their plausible mechanistic roles in inflammatory cascades and tissue injury, yet their clinical value in AECOPD remains insufficiently characterized [4,5,6].

Resistin, an adipokine and proinflammatory cytokine, has been linked to endothelial dysfunction, cardiovascular injury, and sepsis severity [10,11]. Elevated resistin levels correlate with the extent of multi-organ failure and short-term mortality in critical illness, suggesting a potential role in predicting poor outcomes in COPD exacerbations where systemic inflammation predominates [4,5,10,11].

CC16, is produced by non-ciliated bronchiolar epithelial cells and functions as an anti-inflammatory and epithelial-protective factor [6,12]. Decreased CC16 concentrations have been associated with epithelial barrier disruption, pulmonary hyperpermeability, and increased susceptibility to airway injury. In COPD, CC16 deficiency correlates with accelerated disease progression and poorer lung function indices, making it a potential marker of respiratory epithelial integrity [6,12].

IL-6 and tumor necrosis factor-alpha TNF-α are well-established mediators of systemic inflammation and have been consistently associated with disease severity and exacerbation frequency in COPD [13,14,15]. Both cytokines drive neutrophilic inflammation and contribute to skeletal muscle wasting, oxidative stress, and vascular dysfunction. Elevated IL-6 and TNF-α levels at exacerbation onset have been shown to predict adverse clinical outcomes and increased mortality, underscoring their potential role in biomarker-based prognostic models [13,14,15].

S100β protein, a calcium-binding glial marker, reflects astrocytic activation and neuronal injury. Although traditionally studied in acute brain injury and cardiac arrest survivors [16,17], S100β may also indicate cerebral hypoxia secondary to respiratory failure in severe COPD exacerbations. Elevated serum levels could thus signify subclinical neurological impairment, contributing to poor recovery and increased mortality in critical COPD cases [16,17].

Despite this growing body of evidence, no comprehensive study has yet examined the combined prognostic value of these biomarkers in AECOPD patients presenting to the Emergency Department. Integrating inflammatory, epithelial, and neuroinjury markers into a single prognostic framework could bridge the existing gap between clinical assessment and pathophysiological reality, providing a more nuanced understanding of disease severity and recovery potential.

The proposed study seeks to validate the prognostic significance of resistin, CC16, IL-6, TNF-α, and S100β in a real-world emergency care population. By correlating their serum concentrations with established clinical scores, imaging parameters, and short-term outcomes, this research aims to identify biomarker thresholds predictive of mortality and ventilator support escalation. Ultimately, these findings could support the development of a biomarker-based early prognostic score, offering a precision-medicine approach to COPD management in the ED (Table 1). Specifically, we will evaluate whether baseline biomarker concentrations obtained at ED admission correlate with the subsequent level of respiratory support required during hospitalization, supplemental oxygen, non-invasive ventilation (NIV), or invasive mechanical ventilation (IMV), without influencing therapeutic decisions in real time.

## 2. Materials and Methods

### 2.1. Study Design and Setting

This research is designed as a prospective, analytical, longitudinal, multicenter observational study conducted by an institutional consortium including the “Iuliu-Hatieganu” University of Medicine and Pharmacy Cluj-Napoca and affiliated hospitals: County Emergency Clinical Hospital Cluj-Napoca (primary site), Municipal Clinical Hospital Cluj-Napoca, Clinical Hospital of Infectious Diseases Cluj-Napoca, Leon Daniello Pneumology Hospital Cluj-Napoca, and “[name]” Military Emergency Hospital Cluj-Napoca, all equipped with intensive care units for the admission of critically ill patients and dedicated wards for non-critical COPD patients.

### 2.2. Study Population

The target population consists of adult patients (≥ 50 years) with a previous diagnosis of COPD presenting to the ED with an acute exacerbation requiring evaluation and management. Acute exacerbations will be defined according to the Rome Proposal, which defines an acute exacerbation as an event characterized by worsening dyspnea and/or cough and sputum over ≤14 days, often accompanied by tachypnea and/or tachycardia, and associated with increased local and systemic inflammation and physiological deterioration [18,19]. Exacerbation severity will be classified at the point of care as mild, moderate, or severe according to the Rome Proposal severity classification, based on objective clinical, physiological, and inflammatory parameters assessed at ED presentation [18,19]. Patients enrolled in the study will have a prior diagnosis of COPD, with GOLD spirometric grade and ABE category assessment established according to current GOLD recommendations at the Pneumology Clinic. The GOLD spirometric grades (I–IV) classify the physiological severity of airflow obstruction and are defined based on post-bronchodilator forced expiratory volume in 1 s (FEV_1_) expressed as percent predicted. This spirometric grading remains a fundamental descriptor of disease severity and is essential for the diagnostic characterization of COPD. Category A includes patients with low symptom burden and low risk of exacerbations. Category B includes patients with increased symptoms but low risk of exacerbations. Category E includes patients at high exacerbation risk, irrespective of the level of symptoms [3] (Table 2).

Patients presenting with conditions that mimic an acute COPD exacerbation will be excluded from the study. These include acute heart failure, acute coronary syndromes, major arrhythmias, pulmonary embolism, pneumothorax, acute asthma exacerbation, non-pulmonary sepsis, upper airway obstruction, and respiratory infections in patients without previously documented COPD. Additional conditions that may interfere with respiratory function and therefore lead to exclusion from the study are detailed in Table 3. In patients presenting to the ED with a previously confirmed diagnosis of COPD, infections such as pneumonia, bronchitis, or viral illnesses will be considered valid triggers of an acute exacerbation [18,19].

### 2.3. Sample Size and Study Duration

The study is planned to include approximately 100 consecutive eligible patients admitted over a 15-month period. The sample size was estimated based on local patient volumes and previous annual ED statistics (over 600 COPD admissions per year), ensuring sufficient statistical power to detect correlations between biomarker levels and clinical outcomes. Baseline biomarker values will be analyzed exclusively for prognostic correlation with the later need for oxygen therapy, NIV or IMV, and will not be used to guide acute therapeutic escalation or de-escalation.

Based on an estimated annual number of approximately 600 COPD presentations to the ED, we anticipated enrolling around 100 eligible patients meeting the study inclusion criteria. In these participants, five biomarkers (resistin, CC16, IL-6, TNF-α, and S100β protein) will be measured and correlated with disease severity and short-term outcomes.

A post hoc power analysis performed using G*Power software (version 3.1.9.7) for a two-tailed Mann–Whitney test, assuming a large effect size (Cohen’s d = 0.8) and a Bonferroni-adjusted significance level (α = 0.01), indicated a statistical power (1 − β) of approximately 0.91–0.92. This suggests that a sample size of 100 participants could be adequate for detecting large and clinically relevant differences in biomarker levels between well-defined severity or outcome groups. In patients with acute exacerbations of COPD, Vassiliou et al. reported higher serum resistin levels during the acute phase as compared to the stable phase after clinical recovery (median at admission 19.44 ng/mL vs. 9.70 ng/mL at follow-up), indicating a large difference between clinically distinct states [4]. We will reevaluate the sample size after enrollment of 20 patients, and we plan to extend the study to other centers, if necessary.

### 2.4. Ethical Considerations

The study has received ethical approval from the Ethics Committee of “Iuliu-Hatieganu” University of Medicine and Pharmacy Cluj-Napoca (No. AVZ 71/20 March 2025) and from the Ethics Committee of Cluj-Napoca County Emergency Clinical Hospital (No. 9333/17 March 2025). The study will comply with the Declaration of Helsinki, the European Union General Data Protection Regulation, and national research ethics legislation. All participants (or their legal representatives) will provide written informed consent prior to enrollment.

### 2.5. Data Collection Procedures

#### 2.5.1. Therapeutic Protocol

All patients will receive therapy appropriate to the stage of COPD and to any acute comorbidities, in accordance with current clinical guidelines. Patients presenting with fever secondary to infectious processes will receive antipyretic therapy according to current standards of care, with the aim of reducing elevated body temperature and restoring normothermia. In critically ill patients with suspected sepsis or septic shock, intravenous administration of isotonic crystalloid fluids, as well as inotropic and vasoactive medications, will be initiated according to the Surviving Sepsis Campain recommendation, with the aim of maintaining a urine output ≥0.5 mL/kg/hour and a mean arterial pressure (MAP) ≥ 70 mmHg, ensuring adequate cerebral perfusion [20]. The choice of vasopressor medication will be at the discretion of the attending physician. Patients requiring non-invasive or invasive mechanical ventilation will receive appropriate ventilatory support as indicated by the attending physician. All patients will undergo routine laboratory testing, as well as specific investigations relevant to their underlying pathology or comorbidities, along with radiologic and imaging studies necessary for optimal case management, at the discretion of the treating physician. Therapeutic decisions will be individualized according to disease severity and patient-specific characteristics, following the current evidence-based guidelines for COPD exacerbations (GOLD), sepsis and septic shock (Surviving Sepsis Campaign), pneumonia, and other acute conditions identified at presentation [3,20,21].

#### 2.5.2. Recorded Data

Demographic data: age, sex, place of residence (urban or rural), living conditions (home or long-term care facility), past medical history, chronic medication, hospitalization within the previous 30 days, and classification as end-stage or palliative care prior to ED admission will be recorded in the patient monitoring form at admission.

Parameters evaluated during the study at ED admission: systolic and diastolic blood pressure (SBP/DBP), mean arterial pressure (MAP), core temperature (T°C), Glasgow Coma Scale (GCS) score, blood glucose, urine output, peripheral oxygen saturation (SpO_2_), end-tidal (Et) carbon dioxide (CO_2_)—EtCO_2_ and EtCO_2_ trend; oxygen therapy requirements [(mask type, O_2_ flow rate per minute, Fraction of Inspired Oxygen (FiO_2_)]; need for NIV with ventilatory parameters; need for IMV with ventilatory parameters, including airway resistance and lung compliance; requirement for vasoactive support; and medication administered in the ED.

Laboratory data collected at ED admission: routine laboratory investigations will be performed at ED admission and will include a complete blood count, serum creatinine, urea, liver enzymes [Alanine Aminotransferase (ALT) and Aspartate Aminotransferase (AST)], total bilirubin, blood glucose, and a standard coagulation profile. Arterial blood gas analysis will be conducted to assess potential of hydrogen (pH), lactate, bicarbonate (HCO_3_^−^), partial arterial pressures of oxygen (PaO_2_) and carbon dioxide (PaCO_2_), fraction of inspired oxygen (FiO_2_), the PaO_2_/FiO_2_ ratio, the end-tidal to arterial CO_2_ gradient (EtCO_2_–PaCO_2_), and the alveolar—arterial oxygen difference (A–aDO_2_). Additional analyses well comprise sepsis and infection biomarkers [C-reactive protein (CRP), procalcitonin, and fibrinogen], cardiac dysfunction biomarkers [high-sensitivity troponin I (hs-cTnI) and N-terminal-pro–B-type-Natriuretic-Peptide (NT-proBNP)], and the thrombosis marker D-dimer.

Imaging studies performed at ED admission: Imaging studies well be performed at ED admission according to clinical indications and will include chest radiography, chest computed tomography (CT), and lung ultrasound examinations. In selected cases, diaphragmatic motion and compliance will also be assessed by bedside ultrasonography to evaluate respiratory mechanics and ventilatory function.

#### 2.5.3. Biomarkers Selected for Assessment in the Study

Serum concentrations of resistin, CC16, IL-6, TNF-α and S100B protein will be measured using standardized sandwich ELISA assays kits (Elabscience^®^, Biotechnology Inc., Wuhan, Hubei, China). Blood samples will be collected at ED admission into 5 mL biochemistry vacutainers with gel separator. After collection, samples will be centrifuged, at 3500 rpm and the resulting serum will be either processed fresh within a maximum of eight hours or stored at −70 °C until analysis, according to the manufacturer’s recommendations. Hemolyzed or lipemic samples will be excluded.

All assays will be performed following the manufacturer’s protocol, including reagent preparation, incubation conditions, calibration curve generation, and internal quality control verification. Optical density will be measured at 450 nm, and biomarker concentrations will be calculated using a four-parameter logistic (4-PL) curve model.

The analytical characteristics of each ELISA assay, detection range, analytical sensitivity (LOD/LOQ), intra- and inter-assay variability (CV%), assay specificity and cross-reactivity, and reference intervals for normal adult populations, are summarized in Table 4.

#### 2.5.4. Data Monitoring

At ED admission, all patients will undergo assessment using validated severity and prognostic scores available on the MDCalc platform (www.mdcalc.com). The following tools will be applied: mMRC Dyspnea Scale for grading dyspnea severity, the SOFA score, GCS, for evaluating neurological impairment secondary to hypoxia or hypercapnia, and the CFS, adapted for triage levels used in Romania, to estimate frailty and predict mortality. Additional prognostic scores specific to COPD will be applied, including the Ottawa COPD Risk Scale (predicting 30-day mortality or severe adverse events such as myocardial infarction or the need for intubation), the DECAF Score for in-hospital mortality in acute exacerbations of COPD, and the BAP-65 Score for in-hospital mortality prediction.

Serum biomarker levels will be measured according to the previously described analytical protocol. Based on clinical status and therapeutic requirements, study participants will be classified into three groups: COPD patients requiring supplemental oxygen therapy, those requiring NIV, and those requiring IMV. These measurements are intended solely to establish prognostic associations with subsequent respiratory support requirements and will not influence real-time clinical management.

At discharge from the ED or before hospitalization in the Pulmonology Department or the Internal Medicine Department, patient outcomes will be documented as improved (reduction in dyspnea and clinical instability, no requirement for escalation of respiratory support, decreased level of respiratory support, and evidence of improving gas exchange), stable (no significant improvement but no deterioration, with the same level of respiratory support maintained), worsened (increased respiratory distress, need for escalation of respiratory support, and worsening gas exchange or hemodynamics), or deceased (ED mortality). The total duration of hospitalization will be recorded, as well as survival time, including the date of death if it occurred during the ED stay or hospitalization. Early survival will additionally be assessed at 28 days through telephone follow-up.

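### The three respiratory-support groups have no time point, do not separate support in place at sampling from later support, and omit patients needing no oxygen

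*Protocol article*

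**What the plan says.** - **Sampling.** Section 2.5.3: blood for the five biomarkers is drawn at ED admission. No later sample is described.
- **Support at the same moment.** Section 2.5.2 lists, among the parameters evaluated at ED admission, the oxygen requirement and "need for NIV with ventilatory parameters; need for IMV with ventilatory parameters".
- **Grouping.** Section 2.5.4: "Based on clinical status and therapeutic requirements, study participants will be classified into three groups", which are oxygen, NIV and IMV. The section does not say when the group is assigned, or whether it is the current or the highest level.
- **Aim.** The Introduction asks whether admission concentrations "correlate with the subsequent level of respiratory support required during hospitalization". Sections 2.3, 2.5.4 and 3 also speak of later support, and section 3 includes progression to supplemental oxygen. The first secondary objective in Table 1 is cut-offs for escalation of support.
- **Who is enrolled.** Table 2 accepts any COPD stage and any ongoing therapy. No criterion requires oxygen or excludes patients already supported. Section 2.2: "Exacerbation severity will be classified at the point of care as mild, moderate, or severe".
- **Other outcome.** Section 2.5.4 also rates each patient as improved, stable, worsened or deceased at ED discharge or before ward admission. Escalation of support is part of the worsened category.
- **Analysis.** Section 2.5.6 plans ROC curves for individual biomarkers against adverse outcomes that it does not specify, and regression adjusted for baseline severity indicators. Support level at sampling is not named among them.

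**The concern.** A prognostic question needs an outcome that arises after the predictor is measured. Here the predictor and the first record of support share a time point, and the grouping does not say which side of it counts. If the groups mean the level at admission, they describe current severity. If they mean the highest level reached, they pool support already present with support started later. Neither reading isolates later escalation, which is what the aim and the cut-off objective require.

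The groups are also not exhaustive. A patient with a mild exacerbation who needs no oxygen is eligible but belongs to none of them, and progression to oxygen cannot be studied without a no-oxygen starting state.

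What is at stake is interpretation. A marker that only tracks how ill the patient is on arrival could be reported as predicting later NIV or IMV, and a cut-off could be derived largely from patients who had already reached that level.

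**Working it through.** **1. The protocol's own figure.** It gives no number for this point. Its only design figure is the power in section 2.3: "approximately 100 consecutive eligible patients admitted over a 15-month period", calculated "for a two-tailed Mann–Whitney test", with d = 0.8 and α = 0.01, giving about 0.91–0.92. The group split is not stated, so 50:50 is assumed here.

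- Normal approximation: Φ(0.8 × √(50/2) − 2.576) = Φ(4.000 − 2.576) = Φ(1.424) = 0.923.
- Noncentral t, 98 df: 0.912.
- Noncentral t with the Mann–Whitney efficiency 3/π: 0.897.

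The stated range is reproduced at 50:50. It does not test the definition of the groups, but its d = 0.8 serves as the effect size below.

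**2. How much current severity could enter the result.** Assumptions, none of them from the protocol: 30 of 100 patients end in the NIV/IMV group; a share s of those 30 was already on NIV or IMV at sampling; the marker is shifted by d = 0.8 in those already supported and carries no information on later escalation.

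- AUC for support already present: Φ(0.8/√2) = 0.714.
- AUC for later escalation: 0.50, by assumption.
- AUC for the pooled group is the case-weighted mean: s × 0.714 + (1 − s) × 0.50.
- Later escalations per 100 patients: 30 × (1 − s).

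| Share s already supported | Apparent AUC | Later escalations per 100 |
|---|---|---|
| 0% | 0.50 | 30 |
| 25% | 0.55 | 22.5 |
| 50% | 0.61 | 15 |
| 75% | 0.66 | 7.5 |
| 100% | 0.71 | 0 |

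A simulation of 400,000 patients per scenario agreed (0.499, 0.554, 0.609, 0.661, 0.715). The AUC for later escalation among patients not yet on NIV or IMV stayed at 0.50 wherever it could be computed. The apparent AUC depends on s, not on the 30%, which affects only the event count.

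**3. What a restricted analysis would have to work with.** Power for later escalators against the rest (N = 100, d = 0.8, α = 0.01, efficiency 3/π):

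| Split | Power |
|---|---|
| 30:70 | 0.83 |
| 25:75 | 0.77 |
| 20:80 | 0.69 |
| 15:85 | 0.57 |
| 10:90 | 0.39 |

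The splits are assumed. Patients already at the target level also leave the comparison, so true power would be somewhat lower. This is the price of an honest answer to the escalation question, not an argument for pooling.

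**The case against.** The strongest defence is that the text leaves the timing open rather than stating that current and later support are mixed. The intent to study later support is written in four sections. This stands: a reader might infer that patients arriving on NIV or IMV will be counted as predicted events, but no sentence says so.

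Second, the worsened, stable and improved categories are relative to earlier support, so a patient on unchanged NIV is not an escalation there, and section 2.5.6 does not say that cut-offs will use the three groups instead. This stands in part. The rating is made at ED discharge or before ward admission, so it cannot answer a question about support during hospitalization.

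Third, support at admission is already recorded and regression adjusts for baseline severity. The record does stand, and it makes the repair cheap. The adjustment does not name support level, and the single-biomarker ROC analysis has no stated restriction to patients who can still escalate.

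Fourth, a reader might infer that deaths without IMV are hidden in a lower support group. The article does not say this. Death is a separate category, its date is recorded, and 28-day survival has its own analysis. How death is combined with support level is commonly left to an analysis plan.

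Finally, could the whole point be left to a fuller document? Not entirely. The article itself fixes three groups for all participants, and those groups do not fit its own eligibility and aims.

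**Conclusion.** The point holds as a defect of definition. The three groups lack a time point, do not separate support present at sampling from later support, and leave patients needing no oxygen unclassified. Results based on them could partly reflect severity at arrival.

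The size cannot be fixed from the article, because the share already on NIV or IMV at sampling is not given. Under the assumptions shown, the apparent AUC for a marker with no forward value lies between 0.50 and 0.71. At a share of zero there is no distortion. A reader might take a single value from that range as the expected bias, or conclude that prediction necessarily turns into description. The documents support neither, since both the share and the absence of forward value are assumed.

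The primary objective, discharge status and 28-day survival, is not defined by these groups. This concerns a secondary objective and should be fixed. It does not undermine the study.

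**What to change.** 1. Define the respiratory-support outcome as the highest level reached after blood sampling and up to hospital discharge.
2. Add a no-oxygen category so that every participant is classified.
3. Use the support level already recorded at ED admission as the baseline, confirming that it refers to the time of the blood draw.
4. Derive each escalation cut-off only in patients below the target level at sampling.
5. Adjust the association models for baseline support level.
6. Report deaths without IMV separately or in a sensitivity analysis. An ordinal model, or ranking death as the worst category, is an option rather than a requirement; with about 100 patients some levels may be sparse.

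**Cost.** Mostly wording. One data field for peak in-hospital support may be needed, because the article lists support at ED admission and a rating at ED exit but no later level, although Table 1 mentions level and duration of ventilatory support. Fewer patients will be evaluable for the cut-offs, with the loss of power shown above. Data collection is under way, so the field is best added now; the timing of support may be hard to recover later.
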